## Abstract

Introduction

The lack or complete loss of all-natural teeth is known as edentulism, and it happens frequently. One of the most prevalent issues among edentulous patients is severe resorption of the residual alveolar ridge, which can still occur even with cautious prosthetic treatment. Therefore, one of the biggest issues faced in dentistry today is retention and stability in the rehabilitation of completely edentulous patients using complete denture prostheses. This problem was resolved by using denture adhesives. Studies show that when denture adhesive is applied correctly, it improves stability and effectiveness for individuals wearing complete dentures by increasing the surface tension between the alveolar mucosa and the denture fitting surface. The denture adhesive must possess safety, cost-effectiveness, and sufficient antibacterial and antifungal properties. The application should be easy, without causing any mess, and have a pleasant smell. It should not alter or obstruct the denture's intaglio surface. Nowadays, it is acknowledged that denture adhesives are treatments that can be used in association with dentures.

Methods

Based on the type of denture adhesive, the patients will be randomly divided into two groups, i.e., 20 patients in each group: Group A (herbal denture adhesive without essential oil) and Group B (herbal denture adhesive with essential oil). The patients will be requested to fill out the questionnaire for masticatory efficiency, retention, stability, etc., at the time of denture insertion without using denture adhesive and seven days after the use of denture adhesive.

Expected results

The overall satisfaction of complete denture patients will be significantly increased when an herbal denture adhesive infused with essential oil is used. This will result in increased stability, retention of the mandibular denture, improved masticatory efficiency, and patient satisfaction.

Conclusions

Patients who are elderly may experience physical and psychological challenges when adjusting to new or relined dentures. Denture adhesive, however, can aid in the patient's satisfaction with the prosthesis' altered occlusion and fit. It also makes the patient feel more confident and secure. A dental professional must be consulted before using denture adhesive.

## Introduction

Edentulism, defined as the absence or total loss of natural teeth, is a common occurrence. Severe alveolar ridge atrophy is a common problem in edentulous patients, and it can occur even in the case of meticulous prosthesis management. As a result, one of dentistry's biggest concerns is the rehabilitation of completely edentulous individuals. A complete denture prosthesis is the most commonly used method for the rehabilitation of completely edentulous patients. Retention and stability are the biggest challenges faced by the dentist in the case of resorbed and compromised ridges; dentists address this issue by using denture adhesive to enhance denture adherence and retention [1]. Studies show that when denture adhesive is applied correctly, it improves stability and effectiveness for individuals wearing complete dentures by raising the surface tension between the alveolar mucosa and the denture fitting surface. Denture adhesives need to be strong, reasonably priced, and possess adequate antibacterial and fungal properties. It should also flavor and smell excellent, be easy to use and obtain, and should not change or damage the intaglio surface of the denture [2]. It is increasingly recognized that denture adhesives are treatments that can be utilized in addition to dentures. A denture adhesive can help an older patient acclimatize to the changing shape, fit, and occlusion of their prosthesis, as it can be difficult for them to adjust both physically and emotionally to new or relined dentures. The patient feels more secure and content when using denture adhesive. However, it is imperative to consult with a dental professional before using denture adhesive [3].

Denture adhesives are categorized based on their forms, such as powder, tapes, gels, and paste. Denture adhesive enhances retention, lessens denture soreness, avoids strangling the mucosal blood supply, and lessens the need for adjustments even when the denture fits [4]. Additionally, there have been reports of improvements in biting force and chewing efficiency, which lead to a wider dispersion of occlusal forces over the tissues supporting the denture and a decrease in local pressure. The lubricating and cushioning properties of adhesives lessen friction and discomfort in the mucosa. Denture adhesives can be very beneficial for patients with muscle control deficiencies caused by hormonal or neurotransmitter abnormalities [5]. This study aims to evaluate and compare two different types of commercially available herbal denture adhesives with regard to patient satisfaction with denture retention.

## Materials and methods

Method

This experimental study will be conducted in the Department of Prosthodontics, Sharad Pawar Dental College and Hospital, Sawangi (M), Wardha, India. The data will be collected in the postgraduate clinic of the Department of Prosthodontics. On the basis of the inclusion and exclusion criteria (Table 1), the patients will be divided randomly into two groups: Group A (n=20) (herbal denture adhesive without essential oil) and Group B (n=20) (herbal denture adhesive with essential oil). A total of 16 closed-ended questions will be asked of patients: eight during denture insertion without using denture adhesives and eight questions seven days after using denture adhesives.

**Table 1 TAB1:** Inclusion and exclusion criteria

Inclusion Criteria	Exclusion Criteria
Patients who are first-time denture wearers	Patients with tooth-supported overdentures
Patients who are old complete denture wearers	Patients with implant-supported overdentures
Patients who are willing to participate in the study	Patients with a single complete denture

The denture adhesive will be fabricated by utilizing carboxymethylcellulose with flavor, mineral oil, petroleum, silica particles, and mesoporous nanoparticles of the selected essential oil (cinnamon oil) with antimicrobial action incorporated into a gel for prolonged release, giving better effectiveness. In order to gather information about denture fitting, removal, chewing, retention, and phonetics, a standard questionnaire form will be given to each patient. Following the patient's answer to Questionnaire 1 (Table 2), a clinical examination and application of denture adhesive demonstration will take place, adhering to the guidelines provided by the manufacturer. The patients will be provided with an explanation of the cleaning routine and the administration of denture adhesive for the next seven days. The patients will be contacted back a week later to complete an additional questionnaire (Table 3) in which they will be asked to rate the denture's strength, biocompatibility, convenience, and masticatory abilities using the glue that was provided.

**Table 2 TAB2:** Questionnaire 1 (at the time of denture insertion) Reference: [1,6,7]

Sr. No.	Questions	Options	No. of Patients
1.	To what extent do you find the retention of your upper denture satisfactory?	Dissatisfied	
		Neutral	
		Satisfied	
2.	To what extent do you find the retention of your lower denture satisfactory?	Dissatisfied	
		Neutral	
		Satisfied	
3.	To what extent do you find the chewing ability of your denture satisfactory?	Dissatisfied	
		Neutral	
		Satisfied	
4.	To what extent are you happy with the comfort of your new denture?	Dissatisfied	
		Neutral	
		Satisfied	
5.	To what extent do you find the speech and sound produced by the denture satisfactory?	Dissatisfied	
		Neutral	
		Satisfied	
6.	How satisfied are you with the way your dentures fit and removal?	Dissatisfied	
		Neutral	
		Satisfied	
7.	Does your denture harm the soft tissues in any way?	Yes	
		No	
8.	Do you have any issues with swallowing because of the denture?	Yes	
		No	

**Table 3 TAB3:** Questionnaire 2 (after seven days of denture insertion) Reference: [1,6,7]

Sr. No.	Questions	Options	No. of Patients
1.	To what extent are you satisfied with the adhesive's ability to keep your upper denture in place?	Dissatisfied	
		Neutral	
		Satisfied	
2.	To what extent are you satisfied with the adhesive's ability to keep your lower denture in place?	Dissatisfied	
		Neutral	
		Satisfied	
3.	How was your chewing experience after using this denture adhesive?	Worse	
		No difference	
		Better	
4.	For what duration did the denture adhesive work on your dentures?	≤4 hours	
		4-8 hours	
		8-12 hours	
5.	How does this denture adhesive taste?	Bad	
		Neither good nor bad	
		Good	
6.	How did you find it to remove the adhesive from your dentures?	Difficult	
		Neutral	
		Easy	
7.	How did you find it difficult to clean your denture after using the denture adhesive?	Difficult	
		Neutral	
		Easy	
8.	How difficult was it for you to wipe your oral cavity after using the denture adhesive?	Difficult	
		Neutral	
		Easy	

Sample Size

The sample size is determined using the following formula: n = {(Z 1-α/2 + Z 1-β)2 p1(1-p1) + p2 (1-p2)}/(p1-p2)^2^, where the proportion of outcome from group 1 (p1) = 0.37, the proportion of outcome from group 2 (p2) = 0.22, the level of significance (α) = 0.05, power (1-β) = 0.80, Z alpha value = 1.96, Z beta value = 0.84, and the total sample size = 40. The sample size estimation is done at a 95% confidence interval. Each group consists of 20 samples.

Statistical analysis

The statistical analysis will be done using IBM SPSS Statistics for Windows, Version 23 (Released 2015; IBM Corp., Armonk, New York). Descriptive statistics will be used for the mean distribution of both groups, and an independent sample t-test will be used for intergroup analysis between both groups.

Age will be given using mean and standard deviation; however, frequency percentage will be used for qualitative characteristics. The independent t-test will be used to compare age between the two groups, and the Pearson chi-square test or Fisher's exact test will be used to compare all qualitative variables at a significant level of p-value ≤0.05 for all variables. The total of each questionnaire's scores will be used to determine the overall satisfaction with the results. Next, choose the percentage of satisfaction for every patient in both groups. The Wilcoxon signed-rank test will be used to compare patient satisfaction before and after the interview.

Ethical considerations

This study has been approved by the Institutional Ethics Committee of Datta Meghe Institute of Higher Education and Research (DMIHER(DU)/IEC/2024/56) dated May 11, 2024. Participant confidentiality will be maintained, and all procedures will adhere to ethical guidelines for research.

Trial registration

The study is registered with the Clinical Trial Registry-India under the CTRI Registration number CTRI/2024/06/068933, registered on June 14, 2024.

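### The before/after Wilcoxon test cannot separate the adhesive effect from a week of denture wear, so it cannot show that adhesive improves satisfaction over no adhesive

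*Protocol article*

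**What the plan says.** All references are to the protocol article.

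- **Groups (Materials and methods, Method).** Both groups receive an adhesive: "Group A (n=20) (herbal denture adhesive without essential oil") and "Group B (n=20) (herbal denture adhesive with essential oil"). No adhesive-free group, run-in or crossover is described.
- **Timing (same section).** The 16 questions are split as "eight during denture insertion without using denture adhesives and eight questions seven days after using denture adhesives". On the order of events: "Following the patient's answer to Questionnaire 1 (Table 2), a clinical examination and application of denture adhesive demonstration will take place". The first rating therefore precedes any adhesive, and the second follows a week of wear with it. The title of Table 3 counts the seven days from denture insertion.
- **Denture and patients.** An item in Table 2 reads "To what extent are you happy with the comfort of your new denture". Table 1 admits both first-time and old complete denture wearers.
- **Adjustment (Introduction).** Of older patients it says "it can be difficult for them to adjust both physically and emotionally to new or relined dentures".
- **Tests (Statistical analysis).** "The Wilcoxon signed-rank test will be used to compare patient satisfaction before and after the interview". Separately, an independent t-test is named for comparing the two groups, and a chi-square or Fisher test for the qualitative variables.
- **Expected claim (Abstract, Expected results).** "The overall satisfaction of complete denture patients will be significantly increased when an herbal denture adhesive infused with essential oil is used". The Results section extends the expectation to comfort, stability and retention.

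**The concern.** The Wilcoxon test is the only one that the article ties by name to patient satisfaction. Its two time points differ in two respects at once: adhesive (none, then seven days of use) and experience with the denture (the moment of insertion, then a week of wear). Chewing, speech and swallowing can hardly be judged at insertion. A change in rating may reflect the adhesive, getting used to the denture, sore spots that develop with wear, or any mixture of these.

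The expected results are worded as an increase in satisfaction when the adhesive is used, with no comparator stated. If a significant before/after result were offered in support, it would be read as adhesive against no adhesive. The trial has no data that could establish that.

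**Working it through.** **1. What each comparison holds constant**

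| Comparison | Adhesive differs? | Time wearing the denture differs? | Randomised? |
|---|---|---|---|
| Before versus after, within patient | Yes: none, then adhesive | Yes: insertion, then seven days | No |
| A versus B at day 7 | Only in the essential oil | No | Yes |

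In the first row the two factors change together in every patient, so no analysis of these data can separate them. In the second row a week of wear is common to both groups and does not bias the contrast. The same is true of a randomised comparison of change from baseline, or of a baseline-adjusted comparison.

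**2. How easily wear alone could give significance (assumed figures, not from the article)**

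Suppose the adhesive has no effect and each changed rating moves by one step. If 8 of 20 patients improve, 1 worsens and 11 do not change, the exact sign test on the 9 changes gives p = 2 × (1 + 9)/2^9 = 20/512 = 0.039. With all changes of equal size, the exact signed-rank test is this same test.

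That is one chosen outcome. Over a range of assumed rates, the chance of an exact two-sided p ≤ 0.05 with no adhesive effect is:

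| Improve / worsen through wear alone | n = 20 (one group) | n = 40 (both groups) |
|---|---|---|
| 20% / 20% | 1.9% | 2.9% |
| 30% / 10% | 17.4% | 44.0% |
| 40% / 10% | 36.7% | 74.2% |
| 50% / 10% | 57.3% | 91.3% |

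By symmetry, the same probabilities apply to a significant fall if the improving and worsening rates are swapped. A week of wear could therefore also hide a real benefit.

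**3. What the randomised comparison can deliver**

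Inputs from Sample Size: p1 = 0.37, p2 = 0.22, z values 1.96 and 0.84, total 40, 20 per group.

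- Sum of variances: 0.37 × 0.63 + 0.22 × 0.78 = 0.2331 + 0.1716 = 0.4047.
- The article's formula, bracketed in the usual way: (1.96 + 0.84)² × 0.4047 / 0.15² = 7.84 × 0.4047 / 0.0225 = 141.0, so 142 per group. The stated 20 per group does not reproduce.
- Power at 20 per group, two-sided: the standard error under the alternative is √(0.4047/20) = 0.1422. The pooled proportion is 0.295, so the null standard error is √(2 × 0.295 × 0.705/20) = 0.1442. Then (0.15 − 1.96 × 0.1442)/0.1422 = −0.93, and power is 17.6%.
- Half-width of a 95% CI for the difference at these proportions: 1.96 × 0.1422 = 0.279, or about 28 percentage points.

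**The case against.** **The between-group comparison is already planned.** The Introduction gives the aim as comparing two herbal adhesives, and the Statistical analysis section names between-group tests. This stands, and the fix relies on it. The article does not, however, say that the satisfaction conclusion rests on those tests. The test it names for satisfaction is the before/after one.

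**The expected results can be read as B versus A.** They concern the essential-oil product and are not explicitly linked to the Wilcoxon result. That reading is possible, but no comparator is stated and the wording is of an increase. The ambiguity is the reason to reword.

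**Adaptation is not shown to raise ratings.** A reader might infer from the Introduction that satisfaction improves in the first week without adhesive. The text does not say so. It says that adjusting can be difficult and that an adhesive can help. The direction of the bias is unknown, and old denture wearers, who are eligible, probably adapt less. Neither point makes the change attributable to the adhesive.

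**Separate tests by group.** A reader might also infer that significance in B but not in A will be taken as superiority of B. That would be invalid, but nothing in the article says that it will be done, or that the Wilcoxon test will be run by group.

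**The same test has another weakness.** The two questionnaires share only upper retention, lower retention and chewing as topics, and the second rewords these around the adhesive. This is a separate reason not to read the paired difference as a treatment effect. The present point does not depend on it.

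**Conclusion.** The point holds for the before/after comparison. By design, that comparison confounds the adhesive effect with a week of denture wear, and it cannot support a claim that adhesive improves satisfaction over no adhesive. This follows from the stated groups and timing and needs no numerical assumption. The size and direction of the bias cannot be derived from the article; the 17-57% (n = 20) and 44-91% (n = 40) figures rest on assumed rates and show only that the bias could matter.

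It would go too far to conclude that the trial has no valid comparison. The randomised A-versus-B contrast is not biased by adaptation and can address what the essential oil adds. It is weak at this size: about 18% power if the article's own proportions are true.

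**What to change.** 1. In Statistical analysis, state that the conclusion on satisfaction rests on the randomised comparison of group A with group B at day 7, reported as a difference with its 95% CI.
2. Label the within-patient Wilcoxon result descriptive, and say that it reflects adhesive use and a week of wear together.
3. Reword the expected results in the Abstract and in Results as group B against group A. Draw no claim of adhesive against no adhesive from the pre/post change.

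No further patients, visits or procedures are needed for these changes. The cost is that the sponsor gives up the pre/post efficacy claim and is left with a comparison of low power. The article should say so openly, so that a non-significant A-versus-B result is not read as equivalence.

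### The A versus B comparison is valid but leaves unused the baseline answers and wearer type the trial already has, at a modest cost in precision

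*Protocol article*

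**What the plan says.** All places are in the protocol article, Materials and methods.

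- **Eligibility (Table 1).** Both "Patients who are first-time denture wearers" and "Patients who are old complete denture wearers" may enter. No quota or expected split is given.
- **Allocation (Method).** "the patients will be divided randomly into two groups: Group A (n=20") and Group B, also of 20. No stratification factor is named.
- **Data (Method, Tables 2 and 3).** Patients answer closed questions twice: "eight during denture insertion without using denture adhesives and eight questions seven days after using denture adhesives". Questionnaire 1 covers upper retention, lower retention and chewing, among other items. Questionnaire 2 returns to those three topics but otherwise asks about the adhesive itself (duration, taste, removal, cleaning).
- **Between-group analysis (Statistical analysis).** "an independent sample t-test will be used for intergroup analysis between both groups", and "the Pearson chi-square test or Fisher's exact test will be used to compare all qualitative variables".
- **Score.** "The total of each questionnaire's scores will be used to determine the overall satisfaction with the results".
- **Before and after.** "The Wilcoxon signed-rank test will be used to compare patient satisfaction before and after the interview".

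**The concern.** Two things known about each patient before the adhesive is used could plausibly predict the day-7 answers: prior denture experience and initial satisfaction with retention. The article's Discussion supports the second. It reports a cited study of three adhesive brands in 30 edentulous patients, in which the benefit was most marked where denture retention was poor. Yet none of the tests named for A versus B takes a covariate or a stratum.

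In a trial of 40, a chance difference between arms in either factor shifts the observed A versus B difference, and the stated analysis cannot take that out. Variation that baseline could explain also stays in the error term. Both costs could be reduced with data already in hand.

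**Working it through.** **1. The plan's own figure, for context.** Inputs from Sample Size: 0.37 and 0.22, Z values 1.96 and 0.84, total 40.

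n per group = (1.96 + 0.84)² × [0.37 × 0.63 + 0.22 × 0.78] / 0.15² = 7.84 × 0.4047 / 0.0225 = 141.0, so 142.

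The stated 20 per group is not reproduced. At 20 per group, power for 0.37 versus 0.22 is about 0.18 (normal approximation), 0.19 (exact, chi-square) or 0.11 (exact, Fisher). This is a separate and larger problem; it matters here only because it shows how little precision there is to spare.

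**2. What adjusting a score for baseline could gain.** The correlation r between baseline and day-7 scores is an assumption. Linear adjustment multiplies residual variance by 1 − r², so 20 per arm acts like 20/(1 − r²). The difference detectable at 80% power is 2.802 × √(2/20) × √(1 − r²) standard deviations, which is 0.89 SD unadjusted.

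| r | Residual variance factor | Acts like, per arm | Detectable difference |
|---|---|---|---|
| 0.1 | 0.99 | 20.2 | 0.88 SD |
| 0.3 | 0.91 | 22.0 | 0.85 SD |
| 0.5 | 0.75 | 26.7 | 0.77 SD |

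**3. The cost of the extra terms.** Estimating q covariate coefficients inflates the expected variance of the adjusted difference by about 1 + q/(N − q − 3) (normal covariates). With q = 2 and N = 40 this is 1 + 2/35 = 1.057. If wearer type adds nothing beyond baseline, the net factors are 0.99 × 1.057 = 1.05, 0.91 × 1.057 = 0.96 and 0.75 × 1.057 = 0.79. Break-even is at r² = 1 − 35/37 = 0.054, or r of about 0.23.

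**4. Chance imbalance in wearer type.** The split is also assumed. With unstratified 20:20 allocation, the number of first-time wearers in one arm is hypergeometric.

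| First-time wearers of 40 | P(arms differ by ≥4, i.e. 20 points) | P(differ by ≥6, i.e. 30 points) |
|---|---|---|
| 20 | 0.34 | 0.11 |
| 10 or 30 | 0.27 | 0.06 |

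These are probabilities of imbalance, not of a wrong answer. As an illustration, suppose wearer type shifts a satisfaction proportion by 20 points (assumed). A 20-point imbalance then moves the A versus B difference by 0.20 × 0.20 = 4 points. The sampling standard error at the planning proportions is √(0.4047/20) = 0.142, about 14 points.

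**5. Whether adjustment rescues the sample size.** On the variance scale, 20 per arm would need r = √(1 − 20/141.0), about 0.93, to do the work of 141. At r = 0.5, approximate power for 0.37 versus 0.22 rises only from 0.18 to about 0.23.

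**The case against.** The strongest reply is that nothing here is invalid. After randomisation, an unadjusted t-test or chi-square test is a legitimate comparison, and its standard error already allows for chance imbalance. That stands. A reader might infer that pooling the two wearer types biases the A versus B result or inflates the false-positive rate; the documents give no support for that.

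Four further points stand in part:

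- **Stratification.** A condensed article may leave allocation details to the full protocol, so its silence does not show that randomisation is unstratified. The firm part is the named between-group tests, which are unadjusted. The t-test's variable is not named, but no use of baseline in it is stated.
- **Baseline comparisons.** It would be wrong to infer that age is the only baseline variable to be compared. The categorical tests are to cover all qualitative variables, which could include wearer type and the Questionnaire 1 items. Testing for imbalance, however, does not adjust the A versus B estimate.
- **Predictive strength.** Baseline may predict weakly. Questionnaire 1 is answered at insertion, day-7 retention items rate the adhesive, and the day-7 chewing item already asks about change. The article does not say that the two wearer types differ in expectations, and its baseline comfort item refers to a new denture, so previous wearers may also be rating one. This is why the range starts at 0.1.
- **Model choice.** A proportional-odds model of a three-level item may be unstable with 40 patients, and the 1 − r² formula does not describe it. That rules it out as the main analysis but does not touch ANCOVA of a score.

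**Conclusion.** The point holds as one of efficiency. The stated A versus B analysis is valid, but it sets aside baseline answers that the trial collects and a wearer status that eligibility reveals. The only stated before/after use is within patients.

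The reduction in residual variance is about 1% to 25% for an assumed correlation of 0.1 to 0.5. After paying for two extra terms there is a real gain only if baseline and wearer type together predict the day-7 score at least modestly (r above about 0.23). Imbalance of 20 points or more in wearer type has a probability of roughly 0.27 to 0.34 for the assumed splits without stratification, but its likely effect on the estimate is small beside the sampling error. Neither the correlation nor the split is in the article. A reader might hope that adjustment would make 40 patients enough; the figures above show that it would not.

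**What to change.** - Replace the unadjusted t-test on the day-7 satisfaction score with a pre-specified ANCOVA containing group, the Questionnaire 1 score and wearer type. Where a retention item is analysed, use its Questionnaire 1 counterpart as the baseline term (item 1 for upper, item 2 for lower).
- Do not use a raw change score, because the two questionnaires ask different things.
- Keep any ordinal model of single items as a sensitivity analysis.
- Show age and the other baseline variables descriptively by group, without significance tests.
- If randomisation has not begun, stratifying it by wearer type is an optional addition that needs two allocation lists instead of one.

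The cost is two model terms (residual degrees of freedom fall from 38 to 36) and recording wearer type for each patient. The downside is a small gain, or none, if answers at insertion predict poorly. The covariates should therefore be fixed before the data are seen, not chosen on the result.

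### The day-7 questionnaire is said to rate biocompatibility, but none of its eight items records early stopping, soreness, comfort or swallowing trouble

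*Protocol article*

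**What the plan says.** All references are to the protocol article; no separate analysis plan is shown.

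- **Period of use (Materials and methods, Method).** After Questionnaire 1, patients are examined, shown how to apply the product, and given an "explanation of the cleaning routine and the administration of denture adhesive for the next seven days".
- **Follow-up (same section).** "The patients will be contacted back a week later to complete an additional questionnaire (Table 3"). No other assessment after the start of home use is described.
- **Stated content of that form (same section).** In it "they will be asked to rate the denture's strength, biocompatibility, convenience, and masticatory abilities using the glue that was provided".
- **Number of questions (same section).** There are 16 closed-ended questions, eight at each time point.
- **Items before adhesive (Table 2).** These include comfort (item 4), "Does your denture harm the soft tissues in any way" (item 7) and "Do you have any issues with swallowing because of the denture" (item 8).
- **Items at day 7 (Table 3).** These are upper hold, lower hold ("To what extent are you satisfied with the adhesive's ability to keep your lower denture in place"), chewing, duration of effect, taste ("How does this denture adhesive taste"), removing the adhesive, cleaning the denture and cleaning the mouth.
- **Analysis (Statistical analysis).** Overall satisfaction comes from summing each questionnaire's scores, with a satisfaction percentage for each patient in either group.
- **Arms.** Group A receives the herbal adhesive without essential oil and Group B the one with it, 20 patients each.

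**The concern.** The two products are distinguished by an essential oil, so a natural question about A versus B is whether that ingredient is tolerated as well as the product without it. Two signals would answer it in a seven-day home-use study: whether patients kept using the product, and whether they had soreness, discomfort or swallowing trouble while using it. The printed day-7 form asks for neither.

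This is more than detail left to a fuller document. The article fixes the number of questions and prints every one. An analysis plan can set rules for data that exist, but it cannot analyse an answer that was never requested, and seven-day recall cannot be recovered once the visit has passed.

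At stake is the reading of the satisfaction comparison. If one arm irritates more, its total need not show it. The article's Results section also expects better overall comfort and fewer denture sores with the essential-oil product, and the day-7 form as printed has no item that could support or refute either expectation.

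**Working it through.** **Step 1: set the two forms side by side (Tables 2 and 3).**

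| Topic | Questionnaire 1 (no adhesive) | Questionnaire 2 (day 7) |
|---|---|---|
| Upper hold | item 1 | item 1 |
| Lower hold | item 2 | item 2 |
| Chewing | item 3 | item 3 |
| Comfort | item 4 | none |
| Speech | item 5 | none |
| Fit and removal of denture | item 6 | none |
| Soft-tissue harm | item 7 | none |
| Swallowing | item 8 | none |
| Duration of effect | none | item 4 |
| Taste | none | item 5 |
| Removing adhesive, cleaning denture, cleaning mouth | none | items 6, 7, 8 |
| Used on all days, stop day, reason | none | none |

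The three items closest to biocompatibility (comfort, soft-tissue harm, swallowing) are all on the form completed before exposure and all absent from the form completed after it. Taste is the only tolerability-related item at day 7. The Method text and Table 3 therefore disagree on what the day-7 form measures.

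**Step 2: what the total can register.** Take a patient who stops on day 2 because of soreness but whose denture held well until then. That patient can truthfully answer Satisfied, Satisfied, Better, 8-12 hours, Good, Easy, Easy, Easy. This is the most favourable option on eight of eight items (taking the longest duration as most favourable). Soreness and stopping take nothing off the total, because no item refers to them. Less favourable answers are equally open to the same patient, so a good score is possible and not certain.

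**Step 3: scale.** The documents give no stopping rate, so the size of a bias cannot be computed. The arithmetic below only shows how much one arm's rate on a binary item (satisfied or not) could depend on patients who stopped.

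- One patient in an arm of 20: 1/20 = 5 percentage points.
- Difference used for the sample size: 0.37 - 0.22 = 0.15, which is 0.15 × 20 = 3 patients. The outcome these proportions refer to is not named.
- Let k of 20 patients in one arm stop for intolerance, and let a share s of the other 20 - k be satisfied. The rate is s if the k are left out, s(20 - k)/20 if they count as not satisfied, and [s(20 - k) + k]/20 if they all answer Satisfied. The last two differ by k/20, whatever s is.

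With s = 0.75 (assumed) and k from 1 to 4 (assumed):

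| k | left out | not satisfied | answer Satisfied | spread k/20 |
|---|---|---|---|---|
| 1 | 75% | 71.25% | 76.25% | 5 points |
| 2 | 75% | 67.5% | 77.5% | 10 points |
| 3 | 75% | 63.75% | 78.75% | 15 points |
| 4 | 75% | 60% | 80% | 20 points |

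At k = 3 the spread equals the 0.15 used for planning, but only because k = 3 was assumed. The spread also compares two extremes, and it applies to an item-level rate. It does not carry over to the summed score, whose item scoring is not given.

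**The case against.** The strongest reply is that the article condenses a full protocol that is not shown. Adverse-event recording, reasons for discontinuation and rules for missing questionnaires are commonly kept in the full protocol, the case report form or an analysis plan. Nothing says that Table 3 is the only record made at day 7, or that no other contact takes place. This stands for handling rules and for safety recording, and their absence here is no finding. It does not remove the mismatch between the Method text, which says the day-7 questionnaire rates biocompatibility, and the printed form, which does not.

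A second reply is that the stated aim is satisfaction with retention, so a truthful Satisfied from someone who stopped is a valid answer. That is fair. Letting intolerance override such an answer is a choice of estimand, and it does not fit naturally with a summed score. It supports recording tolerability beside satisfaction rather than folding it in.

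A reader might infer more than the documents support:

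- *That intolerance is counted as success.* No text defines success or codes a stopper as one. Dissatisfied, Worse, the shortest duration, Bad and Difficult are all available and presumably lower the total.
- *That patients who stop or do not return are lost from the comparison.* No text plans an analysis restricted to those who tolerated the product, and the Statistical analysis section speaks of a percentage for each patient in either group.
- *That taste problems go unrecorded.* Item 5 asks about taste and offers Bad. Only stopping because of taste has no place on the form.

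**Conclusion.** The point holds in limited form. Questionnaire 2, the only day-7 instrument described, cannot register incomplete use, soreness, discomfort or swallowing trouble, and this contradicts the statement that it rates biocompatibility. Because satisfaction is a total of the printed items, a patient who stopped for irritation can score well, and a tolerability difference between the arms could go unseen.

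The direction and size of any bias are unknown. Each such patient is worth 5 percentage points of an arm on a binary item. Anything beyond that rests on assumed stopping rates. The conclusion assumes that the eight printed items are the whole form, as the stated count of questions indicates, and that no other day-7 instrument captures these answers.

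The documents do not support the stronger claim that the plan converts intolerance into success or discards it. The change is worth making before the first day-7 visit because it is cheap and the answers cannot be obtained afterwards by analysis.

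**What to change.** 1. Add one line on use to Questionnaire 2, for example: *Did you use the adhesive on all seven days? If not, on which day did you stop, and why?* Offer closed reasons: soreness or burning, taste, swallowing, did not hold, other.
2. Repeat the comfort, soft-tissue and swallowing items from Questionnaire 1 at day 7 for all patients, worded to cover the time the adhesive was in use. Asking only those who stopped would miss a patient who bore soreness for the full week.
3. Seek Questionnaire 2 from every randomised patient, whether or not still using the product, and analyse by allocated arm.
4. Report stops with reasons, and the tolerability answers, per arm beside the satisfaction result. State whether the added items enter the total; keeping them outside it leaves the planned score unchanged.
5. Scoring a stop for intolerance as not satisfied can be a sensitivity analysis on the item-level rates. It need not be the main rule.
6. Bring the Method text and Table 3 into agreement on what the day-7 form measures.

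Cost: one use line plus three repeated items, so Questionnaire 2 goes from 8 to 8 + 1 + 3 = 12 questions and the stated total from 16 to 20, with a few sentences of analysis text. The downside is a slightly longer form and results that may look slightly less favourable.
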